## 3.1 Overall study design and flow chart

Patients will receive lapatinib monotherapy 1500 mg/day for a period of at least one month depending on their response and the clinical status of their disease.

- In this pilot study 20 women with metastatic breast cancer who have circulating occult tumour cells in the blood (defined as the presence of ≥ 1 CTC/ 106 PBMCs detected by immunofluorescence microscopy) despite previous chemotherapy and hormone therapy will be treated with lapatinib. All patients will be enrolled in the Medical Oncology Unit at the University Hospital of Heraklion
- All patients will receive lapatinib for a minimum of one month unless clinical disease progression (defined by RECIST criteria) occurs at an earlier time point. At the end of each month period patients will be assessed for the presence of CTCs and treatment will be administered accordingly as described above.
- Open label trial
- Non randomised
- Primary outcome variable: effect of lapatinib on tumor cells circulating in the blood of breast cancer patients
- Target patient population: Patients with metastatic breast cancer who have been previously treated with chemotherapy and/ or hormonal therapy
- Treatment with lapatinib monotherapy 1500 mg/day

Study flow chart is presented in Table 4.

## Table 4. Study design and flow chart

| **SCREENING PERIOD DAY -21 to 0**  Patient informed consent; past medical history; demography; tumour assessment (chest X‑ray, computerised tomography [CT] scan and bone scan), CTCs assessment (double staining immunofluorescence microscopy for HER2/cytokeratin) |
| --- |
|  |
| **MAIN TREATMENT PERIOD (1 MONTH)**  Patients evaluated for concurrent illness/therapy; physical examination, adverse events at all visits (every month)  Every month: haematology; biochemistry; tumour assessment, CTCs assessment (double staining immunofluorescence experiments)  At 3 months (or at any time in case of suspected clinical disease progression): chest X‑ray, computerised tomography [CT] scan and bone scan) |
|  |
| **SECOND TREATMENT PERIOD**  Patients evaluated for concurrent illness/therapy; physical examination, adverse events at all visits (every month)  Every month: haematology; biochemistry; tumour assessment, CTCs assessment (double staining immunofluorescence experiments)  Every 3 months (or at any time in case of suspected clinical disease progression): chest X‑ray, computerised tomography [CT] scan and bone scan)  . |

Table 5 STUDY PLAN

| Study plan | Screening | Start of treatment | Treatment | | | | | | Discontinuation |
| --- | --- | --- | --- | --- | --- | --- | --- | --- | --- |
| Day (or week) | -21 to  -7 | **0** | +4we | +8we | +12we | +16 we | +20 we | +24 we |  |
| Visit | V1 | V2 | V3 | V4 | V5 | V6 | V7 | V8 |  |
| Informed consent | X |  |  |  |  |  |  |  |  |
| Medical history | X |  |  |  |  |  |  |  |  |
| Pregnancy test (if appropriate) |  | Xa |  |  |  |  |  |  |  |
| Inclusion/exclusion criteria | X | X |  |  |  |  |  |  |  |
| Physical examination including Vital signsb / Performance Status / weight |  | X | X | X | X | X | X | X | X |
| Concurrent medication |  | Xc | X | X | X | X | X | X | X |
| ECG |  | X |  |  |  |  |  |  |  |
| Clinical chemistry/ Hematologyb |  | X | X | X | X | X | X | X |  |
| Tumour assessment | X |  |  |  | X |  |  | X |  |
| CTCs assessment (CTCs number, double staining immunofluorescence microscopy | X | X | X | X | X | X | X | X | X |
| Adverse eventsc |  |  | X | X | X | X | X | X | X,de |
| Dispense study medication |  | X | X |  |  | X |  |  |  |
| Survival |  |  |  |  |  |  |  |  | Xf |

a Pre-menopausal women of child-bearing potential must have a negative urine or serum pregnancy test within 7 days before Day 1 of treatment, In the event of suspected pregnancy during the study, the test should be repeated.

b Laboratory/vital signs abnormalities should not be reported as adverse events (AEs) unless any criterion for a serious adverse event (SAE) is fulfilled, or laboratory/vital signs abnormality causes the subject to discontinue from the study, or the investigator insists the abnormality should be reported as an adverse event.

c In the event of any new or worsening respiratory symptoms (e.g. cough, breathlessness), appropriate medical advice should be sought promptly. Any symptoms should be treated as clinically indicated and reported as an AE or SAE if appropriate.

d Any ongoing study-related toxicity or SAE at discontinuation must be monitored until resolution.

e After discontinuation from treatment, subjects must be followed up for all existing and new AEs for 30 calendar days after the last dose of study drug. All new AEs occurring during that period must be recorded (if SAEs, they must be reported within 24 hours) and followed to resolution where possible.

f After discontinuation from the study for any reason, where possible subject, subject’s family, or the subject’s current physician must be contacted every 8 weeks for survival information until death.

## 3.2 Rationale for study design and dose

Based on preclinical and clinical data, lapatinib is considered a novel and promising therapeutic approach with potential application in the treatment of human breast cancer. Therefore it could be very important and clinically relevant to know if lapatinib is capable of reducing the numbers of occult tumour cells circulating in the blood of breast cancer patients.

Lapatinib will be given at the dose of 1500mg/day for a minimum of 3 months. Results from phase 1 studies support the use of 1500 mg po daily as achieving biologically active concentrations and target pathway inhibition with an acceptable toxicity profile. Phase II studies of lapatinib administered as monotherapy demonstrated that the dose of 1500mg/day was well tolerated and was associated with clinical benefit in patients with breast cancer (27, 29).

The selected patient population is patients with metastatic breast cancer who have received at least one course of standard systemic chemotherapy for their metastatic disease. Prior hormonotherapy is allowed.

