## Table 4. Study design and flow chart………………………………………………………21

Table 5 Study plan…………………………………………………………………..........22

Table 6 Lapatinib starting dose and dose reduction schedule…………………………….32

Table 7 Dose reduction criteria and guideline for management of lapatinib associated toxicity…………………………………………………………………………...32

Protocol synopsis

**A pilot feasibility study to evaluate the efficacy of lapatinib in eliminating cytokeratin-positive tumour cells circulating in the blood of women with breast cancer**

Principal Investigator [name]

Dep of Medical Oncology

University Hospital of Heraklion

Study Chairman: [name]

Professor of Medical Oncology

Dep of Medical Oncology

University Hospital of Heraklion

Study centre(s) and number of subjects planned

This study will be conducted in the Department of Medical Oncology at the University General Hospital of Heraklion, in Greece. Twenty women with metastatic breast cancer are planned to participate in this study.

Objectives

To evaluate the efficacy of lapatinib in eradicating chemo- resistant tumour cells circulating in the blood of patients with breast cancer. These cells will be detected using immunofluorescence microscopy on Peripheral Blood Mononuclear Cell (PBMC) cytospins.

Study design

Open label, single-arm exploratory phase II clinical trial

Target subject population

Patients with metastatic breast cancer who have persistent detection of tumour cells in the peripheral blood (defined as ≥1 CTC per 106 PBMCs detected by immunofluorescence microscopy) despite at least one line of chemotherapy will receive lapatinib for a minimum of one month unless disease progression (defined by RECIST) occurs at an earlier time point. Prior hormonal therapy administered for metastatic disease is allowed.

Investigational product, dosage and mode of administration

Lapatinib 1500 mg/day orally

Duration of treatment

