All patients will receive lapatinib for a minimum of one month unless clinical disease progression (defined by RECIST criteria) occurs at an earlier time point. At the end of the 1-month period patients will be assessed for the presence of CTCs in peripheral blood. Those with decreased or stable CTC counts will continue treatment and will be assessed every month. Patients with increased CTC counts will be withdrawn from the study if further increase is documented at re-assessment after the second treatment course. In subsequent cycles, treatment will be also discontinued in case of two consecutive increases in CTC values. Moreover, treatment will be discontinued in case of disease progression, occurrence of unacceptable toxicity or consent withdrawal, irrespectively of CTC counts.

Outcome variables

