# 3. Study plan and procedures

Patients will receive lapatinib monotherapy 1500 mg/day for a period of at least 1 month (unless disease progression occurs at an earlier time point). Blood samples will be collected at study entry, prior to the first dose and subsequently every month. Tumor assessment by imaging studies will be performed prior to study entry and subsequently every three months. At the end of the first month period patients with will be assessed for the presence of CTCs in their peripheral blood. Patients with decreased or stable CTC counts will continue treatment and will be assessed every month. Patients with increased CTC counts will be withdrawn from the study if further increase is documented at re-assessment after the second treatment course. In subsequent cycles, treatment will be also discontinued in case of two consecutive increases in CTC values. Moreover, treatment will be discontinued in case of disease progression, occurrence of unacceptable toxicity or consent withdrawal, irrespectively of CTC counts.

##

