#### 3.4.1.1 Doses and treatment regimens

1. Lapatinib

Lapatinib is supplied as 250 mg oval, biconvex, orange film-coated tablets. The lapatinib dose level for this study is 1500 mg. The tablets are packaged into HDPE bottles with child-resistant closures. Study treatment will be dispensed to subjects on Day 1 and every monthly visit thereafter until the subject withdraws, or completes the study.

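### The protocol gives two minimum treatment periods (one month and three months) and two dispensing schedules (every monthly visit, or weeks 0, 4 and 16 only); each pair needs reconciling.

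*Protocol*

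**What the plan says.** **Minimum treatment period.** The synopsis, under duration of treatment, states "All patients will receive lapatinib for a minimum of one month", with earlier RECIST progression as an exception. Its target-population paragraph says the same, and so does section 3. Section 3.1 has "Patients will receive lapatinib monotherapy 1500 mg/day for a period of at least one month", and Table 4 labels the main treatment period as one month. Section 3.2, which gives the rationale for design and dose, states "Lapatinib will be given at the dose of 1500mg/day for a minimum of 3 months". It attaches no exception and no explanation.

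**CTC withdrawal rule.** The synopsis and section 3 withdraw a patient whose CTC count has risen at the end of month 1 and rises further at re-assessment after the second course. In later cycles, two consecutive rises also end treatment. Section 3.3.3.1, item 8, lists two consecutive increases as a reason for discontinuation.

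**Dispensing.** Section 3.4.1.1 states "Study treatment will be dispensed to subjects on Day 1 and every monthly visit thereafter", until withdrawal or completion. In Table 5 the row "Dispense study medication" is marked at V2, V3 and V6 only, although visits are scheduled every four weeks from week 0 to week 24. No footnote to Table 5 explains the blank cells.

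**The concern.** A minimum treatment period and a stopping rule have to be capable of being followed together. Here a patient can satisfy the one-month minimum and be withdrawn correctly at about week 8, yet breach the three-month minimum in section 3.2. Staff following section 3.2 would keep that patient on drug; staff following section 3 would withdraw her. In a single-arm study of 20 patients whose primary outcome is the effect of the drug on CTCs, exposure among patients with rising counts should not depend on which page was read.

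The dispensing conflict bears on exposure and on accountability. If a site followed Table 5 with short supplies, some CTC samples would be drawn after time off drug. Section 3.4.1.3 also requires delivery records to be reconciled with usage, and that is harder when the protocol holds two schedules.

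**Working it through.** The protocol states no power or sample-size figure that bears on this point, so there is no figure of its own to reproduce. The check is a side-by-side reading with simple arithmetic.

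**1. Minimum period**

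| Place | Minimum stated |
|---|---|
| Synopsis, target population | one month, unless earlier progression |
| Synopsis, duration of treatment | one month, unless earlier progression |
| Section 3 | one month, unless earlier progression |
| Section 3.1 | one month |
| Table 4, main treatment period | labelled one month |
| Section 3.2 | three months, no exception stated |

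A floor of at least one month does not by itself contradict longer treatment. The test is whether any patient meets one floor and breaks the other while the protocol is followed elsewhere.

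**2. The patient for whom the two floors differ**

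- Count up at the end of month 1 (week 4, V3): treatment continues to a second course.
- Count up again after the second course (about week 8, V4): withdrawn under the synopsis, section 3 and section 3.3.3.1, item 8.
- Exposure at withdrawal is about 8 weeks. This exceeds 4 weeks, so the one-month floor is met. It is short of 12 weeks, so the three-month floor is missed by 12 − 8 = 4 weeks.

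The withdrawal rule and the section 3.2 minimum therefore cannot both be applied to this patient.

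**3. Dispensing marks**

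The Table 5 row has nine data cells under nine header columns, so it has not shifted when the table was read from the PDF. The marks are in columns 2, 3 and 6.

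| Week | 0 | 4 | 8 | 12 | 16 | 20 | 24 |
|---|---|---|---|---|---|---|---|
| Section 3.4.1.1 | yes | yes | yes | yes | yes | yes | if treatment continues |
| Table 5 | yes | yes | – | – | yes | – | – |

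That is 3 marks in Table 5 against 6, or 7 if treatment continues past week 24.

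**4. What the dispensing gap could mean for supply**

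The quantity per dispensing is not stated, so it is treated as an unknown q (weeks of drug). Assume the week-0 supply lasts to week 4 and nothing is carried over between dispensings.

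- Gap between weeks 4 and 16: max(0, 12 − q).
- Gap between weeks 16 and 24: max(0, 8 − q).

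| q (weeks) | Gap before week 16 | Gap before week 24 | Unsupplied |
|---|---|---|---|
| 4 | 12 − 4 = 8 (weeks 8-16) | 8 − 4 = 4 (weeks 20-24) | 12 of 24 weeks |
| 8 | 12 − 8 = 4 (weeks 12-16) | 0 | 4 of 24 weeks |
| 12 | 0 | 0 | none |

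At 1500 mg/day in 250 mg tablets (1500 / 250 = 6 a day), a 28-day supply is 6 × 28 = 168 tablets. The interval from week 4 to week 16 needs 6 × 84 = 504.

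With q = 4, the CTC counts at weeks 12, 16 and 24 would follow time off drug. The four weeks before the counts at weeks 4, 8 and 20 would be supplied.

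**The case against.** The strongest reply is that the minimum has little practical force. Section 3.3.3.1 allows discontinuation at any time and mentions no minimum. Patients with stable or falling counts continue in any case, and so do those with a single rise until the second course. The three-month wording is one sentence in a rationale section against several concordant statements elsewhere. This largely stands: the practical conflict is confined to patients with two rises by about week 8, and it is a reason to grade the point modestly. It does not remove the contradiction, because a count of statements does not amend section 3.2.

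A reader might go further and infer that the first efficacy time point is uncertain, at week 4 or week 12. The documents do not support that. CTCs are assessed at the end of the first month and monthly thereafter, and Table 5 marks them at every visit, whichever minimum is printed. Nor does any section make the minimum a condition for being evaluable. The number of patients progression-free at week 4 or week 12 is likewise the same under either wording, so such counts do not measure this defect.

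On dispensing, it is fair to say that Table 5 may assume larger supplies at weeks 4 and 16, which would leave no gap. That stands as a possibility. It still does not match section 3.4.1.1, and the protocol gives no quantity from which to confirm it.

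**Conclusion.** Both contradictions are in the current text. The minimum period is one month in the synopsis, sections 3 and 3.1 and Table 4, and three months in section 3.2. The three-month statement cannot be met by a patient withdrawn under the CTC rule after the second course. Dispensing is at every monthly visit in section 3.4.1.1 but at 3 visits in Table 5, where the text implies 6 or 7 through week 24.

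The first conflict affects only patients with two consecutive rises by about week 8, whose exposure would differ by about 4 weeks. The second could range from no interruption (12-week quantities at weeks 4 and 16) to 12 of 24 weeks unsupplied (4-week quantities). It would be wrong to read Table 5 as showing that patients will be off drug for half the period, because that rests on an assumed quantity.

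These are drafting inconsistencies in rules that staff must follow. They should be corrected, but they do not undermine the timing of the primary measurement and do not rank with the most serious class of finding.

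**What to change.** Reconcile section 3.2 with the synopsis, sections 3 and 3.1, Table 4 and the CTC withdrawal rule (synopsis, section 3 and section 3.3.3.1, item 8), so that one consistent statement of the minimum period remains and it is clear how it combines with withdrawal. Reconcile the dispensing row of Table 5 with section 3.4.1.1. Which period and which schedule apply is for the sponsor's clinicians; nothing here favours either.

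The cost is a short text correction and, if the table is what changes, one row of Table 5. No change to sample size, visit schedule or CTC sampling follows from this point.

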## 3.3 Selection of study population

### 3.3.1 Inclusion criteria

For inclusion in the study subject must fulfil all of the following criteria:

1. .Provision of written informed consent
2. Histologically or cytologically‑confirmed breast cancer
3. Metastatic breast cancer (stage IIIB and IV). EGFR and/or HER-2 expression on the primary tumor is not mandatory.
4. Patients should have received at least one course of standard systemic chemotherapy for their metastatic disease. Prior hormonal therapy is allowed.
5. Patients should have achieved objective response (CR or PR) or stable disease to previous treatment.
6. There should be at least one month between the end of chemotherapy treatment and trial entry. In case of prior Herceptin administration, 3 months are required to have elapsed before study entry.
7. Detection of at least 1 CTC/106 PBMCs despite the previous administration of chemotherapy and/or hormonal therapy.
8. HER-2 expression on CTCs.
9. Age 18 years and over Adequate organ function

Haematological function:

- Absolute neutrophil count (ANC) ≥1.5 x 109/L
- Platelet count ≥100 x 109/L and
- Haemoglobin ≥9 g/dL (may be transfused to maintain or exceed this level)

Liver Function:

- Total bilirubin <1.5 x upper limit of normal (ULN)
- AST, ALT <2.5 x ULN in patients without liver metastases; <5 x ULN in patients with liver metastases

Renal function:

- Serum creatinine ≤1.25 x ULN or calculated creatinine clearance ≥50 mL/min

1. LVEF within institutional normal range
2. Eastern Cooperative Oncology Group (ECOG) performance status (PS) of 0 to 2
3. Life expectancy of at least 12 weeks

###

### 3.3.2 Exclusion criteria

Any of the following is regarded as a criterion for exclusion from the study:

1. any concurrent systemic treatment for breast cancer (including chemotherapy, radiotherapy, monoclonal antibodies)
2. Other co-existing malignancies or malignancies diagnosed within the last 5 years with the exception of basal cell carcinoma or cervical cancer in situ
3. Any unresolved chronic toxicity greater than Grade 2 (NCI- CTCAE) from previous anticancer therapy (except alopecia)
4. Any evidence of severe or uncontrolled systemic disease (e.g., unstable or uncompensated respiratory, cardiac, hepatic, or renal disease)
5. Pregnancy or breast feeding (women of child-bearing potential). Women of childbearing potential must practice acceptable methods of birth control to prevent pregnancy
6. Treatment with any other investigational agent, or participation in another clinical trial within 28 days prior to enrolment
7. Known hypersensitivity to drugs chemically related to lapatinib
8. Concomitant requirement for medication classified as CYP3A4 inducers or inhibitors.
9. Evidence of any other disease, neurological or metabolic dysfunction, physical examination finding or laboratory finding giving reasonable suspicion of a disease or condition that contraindicates the use of an investigational drug or puts the patient at high risk for treatment-related complications

###

### 3.3.3 Discontinuation of subjects from treatment or assessment

#### 3.3.3.1 Criteria for Discontinuation

Subjects may be discontinued from study treatment and assessments at any time. Specific reasons for discontinuing a subject from this study are:

1. voluntary discontinuation by the subject who is at any time free to discontinue their participation in the study, without prejudice to further treatment.
2. safety reasons as judged by the investigator
3. severe non-compliance to the protocol as judged by the investigator
4. incorrect enrolment of the subject*.*
5. death
6. subject lost to follow-up
7. clinical progression of disease (by symptoms, physical findings, imaging studies)
8. patients with two concecutive increases in CTC numbers

#### 3.3.3.2 Procedures for discontinuation

#### Subjects who discontinue should, if possible, be seen and assessed by an investigator(s). The reason for discontinuation and the date of discontinuation must be documented on the case report form (CRF). If possible any diary cards, questionnaires (e.g. for Quality of Life assessments) and investigational products should be returned by the subject.

All subjects who have new or worsening CTC grade 3 or 4 laboratory values at the time of discontinuation must have further tests performed and the results recorded on the appropriate CRF until the laboratory values have returned to CTC grade 1 or 2, unless these values are not likely to improve because of the underlying disease. In these cases, the investigators must record their opinions on the CRFs and in the subject’s medical records. Laboratory abnormalities should not be reported as adverse events unless any criterion for an SAE is fulfilled, the laboratory abnormality causes the subject to discontinue from the study, or the investigator insists the abnormality should be reported as an AE.

At discontinuation all on-going study-related toxicities and SAEs must be followed until resolution, unless in the investigator’s opinion, the condition is unlikely to resolve due to the subject’s underlying disease.

After discontinuation from treatment, subjects must be followed up for all existing and new AEs for 30 calendar days after the last dose of study drug. All new AEs occurring during that period must be recorded (if SAEs they must be reported within 24 hours) and followed up for resolution as above.

Any subject who withdraws from study treatment for reasons other than progression should continue, where possible, to have objective tumour assessments every 8 weeks in order to collect information on progression of disease.

When disease progression has been documented, the long-term follow up information for survival should be collected at least every 8 weeks by telephone contact with the subject, subject’s family, or by contact with the subject’s current physician.

